## Abstract

**Background/Objectives**: Atopic dermatitis (AD) is a chronic inflammatory skin disease characterized by recurrent rashes and itching, which seriously affects the quality of life of patients and brings a heavy economic burden to society. The treat-to-target (T2T) strategy was proposed to guide optimal use of systemic therapies in patients with moderate to severe AD, and patients’ adherence is emphasized along with combined evaluation from both health providers and patients. While effective treatments for AD are available, non-adherence of treatment is common in clinical practice due to the patients’ unawareness of self-evaluation and lack of concern about the specific follow-up time points in clinics, which leads to the treatment failure and repeated relapse of AD. **Methods**: This project consists of three parts. First, an artificial intelligence (AI) model for diagnosis and severity grading of AD based on deep learning will be trained. Second, an AI assistant decision-making system (AIADMS) in the form of an app will be developed. Third, we design a prospective, randomized controlled trial to test the hypothesis that the AIADMS with implementation of the T2T could help control the disease progression and improve the clinical outcomes. **Results**: A total of 232 participants diagnosed with moderate to severe AD will be included and allocated into the app group or the control group. In the app group, participants will be assisted in using the app during the process of management and follow-up at the scheduled time points, including 2 weeks, 4 weeks, 8 weeks, 12 weeks, 6 months, and 12 months after treatment. In the control group, the diagnosis, treatment, and follow-up of participants will be carried out according to the current routine on a face-to-face basis. The primary outcome is the overall efficiency rate of treating objectives including PP-NRS, EASI, SCORAD, POEM, and DLQI at 12 weeks after treatment, which is calculated as the “Total number of participants with effective treatment of 5 treating objectives/total number of participants *100%”. Spss20.0 software will be used to analyze the data according to the principle of intent to treat. **Trial Registration**: The protocol was registered at the National Institutes of Health Clinical Trials Registry with the trial registration number NCT06362629 on 11 April 2024. **Conclusions**: This study aims to improve AD management by integrating advanced technology, patient engagement, and clinician oversight through AIADMS app to achieve treat-to-target (T2T) goals for effective and safe long-term control.

## 1. Introduction

Atopic dermatitis (AD) is a chronic inflammatory skin disease characterized by recurrent rashes and itching [1]. The prevalence of AD in children is 10–20%, and that in adults is about 1–5% in developed countries. There were 390 million AD patients worldwide in 2019, and the number was estimated to reach 450 million and 520 million by 2024 and 2030, respectively [2]. In 2022, the number of AD patients in China was more than 70 million [3]. For moderate and severe AD, the average course is nearly 10 years, and the overall affected lesion area is more than 30% of the skin. Most patients suffering from AD have difficulty sleeping due to unbearable itching, and reducing itching symptoms is the crucial and urgent need for 75.8% of them. More than 10% of them have suicidal tendencies, and 71.2% of them have experienced discrimination. In addition, more than 75% of dermatologists are not satisfied with the existing treatment plan [4].

AD is primarily driven by the activation of the Th2 immune response, with interleukins (IL)-4 and IL-13 playing central roles in its pathophysiology. Both cytokines are critical in the atopic march and contribute significantly to AD symptoms. IL-4 and IL-13 are encoded by genes on chromosome 5, and their polymorphisms are linked to a genetic predisposition for AD in both children and adults. These cytokines promote Th2 cell differentiation and the production of inflammatory cytokines, which recruit eosinophils, mast cells, and basophils, exacerbating the inflammatory response. IL-4 and IL-13 also contribute to pruritus by stimulating sensory neurons and interacting with the IL-31 pathway. Furthermore, they impair skin barrier function by downregulating epidermal proteins and altering lipid composition, leading to increased transepidermal water loss and susceptibility to infections. IL-13 also plays a unique role in tissue remodeling, promoting collagen production and fibrosis in chronic AD lesions [5].

In August 2022, “Expert Recommendations on Treat-to-Target (T2T) in the Systemic Treatment of Moderate to Severe Atopic Dermatitis” [6] was published, which was combined with the specificities of AD management in clinical practice in China and proposed the treatment objectives and the dynamic adjustment of the treatment plan based on regular follow-up evaluation (Figure 1). The central point of T2T is how to maximize the integration and utilization of relevant resources to help patients achieve persistent control of the disease effectively and safely [7,8]. It is emphasized that the combination of evaluation from both patients and clinicians by applying different evaluative tools, including the Eczema Area and Severity Index (EASI), Patient-oriented Eczema Measure (POEM), Peak Pruritus Numerical Rating Scale (PP-NRS), Scoring Atopic Dermatitis (SCORAD) Index, and Dermatology Life Quality Index (DLQI), which can improve the compliance of patients and provide an important clinical decision-making basis for clinicians [7,8,9]. However, due to the lack of professional medical knowledge and different levels of education, it is difficult for patients to evaluate themselves. Furthermore, clinicians often find it difficult to evaluate patients with all the tools and provide psychological support for patients at clinics because of the limited visiting time. Therefore, the key issues for realization of T2T in AD patients include enhancing the patients’ participation and self-evaluation in systemic treatment, promoting regular follow-up, and effective communication between dermatologists and patients. With the rapid development of mobile technology and artificial intelligence (AI), applications (apps) on smart terminals, including smartphones or pads, with AI assistant decision-making function in the medical field have been explored. Apps can integrate images, documents, videos, and other forms of data and make the communication between doctors and patients effective and convenient, regardless of time and place restrictions. Previous studies have shown that app auxiliary management for diabetes and asthma increase the self-management and participation of patients, significantly promote patients’ compliance, and improve clinical outcomes and prognosis, and 80% of patients believe that this kind of service is a feasible alternative to face-to-face treatment [10,11]. Benefiting from AI deep learning, AD could be diagnosed and evaluated with the utilization of convolutional neural networks (CNNs) models. In a CNN model trained from 4740 clinical images based on the EfficientNet-b4 architecture, AD could be diagnosed with an accuracy of 92.57%, sensitivity of 94.56%, and specificity of 94.41% by the AI dermatology diagnosis assistant in the form of a smartphone-based platform [12]. The severity of AD could be measured objectively after CNN model training by the Inception ResNet-v2 algorithm from a dataset including 9192 cropped AD images [13]. Moreover, SCORAD can be calculated automatically with the application of the Resnet-34 architecture for lesion surface segmentation and the EfficientNet-B0 network architecture for visual sign severity grading [14]. Moreover, recent studies have emphasized the importance of AI in dermatology and other medical fields, further highlighting the potential of AI technologies. Li et al. reviewed the current developments and future trends of AI in dermatological image analysis, identifying key areas where AI could enhance clinical decision-making, particularly in lesion detection and classification [15]. Similarly, Hogarty et al. discussed the broader applications of AI in dermatology and its future directions, noting that AI has become an essential tool in advancing diagnostic precision and personalized treatments [16]. These studies further underscore the relevance of integrating AI into AD management for better patient outcomes. Based on the literature, AI assistant management for AD could be realized in clinical practice to increase diagnostic accuracy and save time for both clinicians and patients. However, to the best of our knowledge, no platform integrating AI deep learning and interactive communication with patients focused on the whole process of AD management including diagnosis, severity evaluation, therapeutic goals, and follow-up has been developed.

In this project, we plan to develop an artificial intelligence assistant decision-making system (AIADMS) in the form of an app based on AI deep learning from massive clinical images of AD target lesions, with implementation of the T2T framework and full follow-up for AD patients. We hypothesize that the goal of the T2T could be better achieved by application of the AIADMS for AD patients, and a clinical randomized controlled trial is designed to verify this assumption.

## 2. Materials and Methods

### 2.1. Automatic Detection and Evaluation of AD Based on AI Deep Learning

#### 2.1.1. Dataset of Atopic Dermatitis

The dataset will be established from more than 10,000 clinical images of AD patients for AI deep learning. Low-quality images, those with resolutions less than 640 × 480 pixel or too unclear to identify the structure of the skin lesions, will be excluded. The images containing the surrounding background will be treated by labeling the border of the body or the limb and cropping the labeled part from the image to include only the AD lesions on the skin, and they will be standardized by an image tagging tool to ensure consistency across the dataset.

#### 2.1.2. Labeling the Clinical Signs of Skin Lesions

The labeling will be completed by three certified dermatologists and three trained algorithm engineers. The dermatologists will label the clinical signs, including erythema, papulation, edema, oozing, excoriation, lichenification, and dryness, and the severity of each sign will be evaluated and labeled on a four-point scale (0: none, 1: mild, 2: moderate, and 3: severe). The result of each clinical sign in an image will be labeled as an example of erythema-2, edema-2, or oozing-3. After labeling the images, the dermatologists and algorithm engineers will verify the quality of the labeled images based on both clinical and labeling rules and cross-validate the accuracy of signs and severity. Images that meet the requirements will be used for model training. During the labeling and model training process, the relevant personnel will be unaware of all the private patient information.

#### 2.1.3. Model Training

The model training will be carried out after labeling of the images. An accurate and efficient semantic segmentation model will be trained to distinguish abnormal skin lesion areas to identify all the clinical signs. A fast and accurate pixel-level skin segmentation model will be trained to determine the ratio of the lesion area to the overall skin area. In addition, an efficient and practical method to convert the segmented skin lesion area into real skin area units will be created to achieve the accurate restoration of the true size as much as possible from the distortion of the skin lesion due to the shooting distance, angle, or automatic enhancement. The dataset will be divided for training, validation, and testing. Images of 6500 of the 10,000 will be used in training and validation of the proposed model, and images of the remaining 3500 of the 10,000 will be used for testing. After training, combined with the different questionnaire items filled out by patients, the evaluative tools including EASI, SCORED, POEM, pp-NRS, and DLQI will be calculated by the model.

### 2.2. Development of the AIADMS App

The app will support the Android system and the IOS system, and it will be designed as two versions for both patients and clinicians with the distinguished login entrance. The fundamental functions of the app will include “Push”, “Reminder”, “Upload”, “Evaluation”, and “Data management” (Figure 2 and Supplemental Figure S1).

The “Push” function is designed to transmit information to patients and medical staff. The pushed information could be received and displayed on the screen of the mobile phone even if the app is not opened and the mobile phone is in the locked screen state, and the users can set the time of receiving the pushed information by themselves. For example, the predetermined time point for follow-up in clinics will be presented as “You should come to see the doctor on next Monday, 25 July 2023.” The “Push” function can activate the use of the app, increase the viscosity of users, and drive the utilization of other functional modules.

The “Reminder” function is mainly used for reminding the patients about taking medicine, uploading photos of skin lesions, self-evaluation, and scheduled follow-up.

The “Upload” function is designed to help patients participate in the systemic treatment. They can upload their photos of skin lesions, the description of progresses of AD, or questionnaires.

The “Evaluation” function is developed to provide information for both patients and medical staff. By uploading photos of skin lesions and filling in the different questionnaire items, the app will automatically evaluate the severity of lesions and calculate the EASI, POEM, PP-NRS, SCORAD, or DLQI scores. This function could help patients know more about their situation related to the disease and take part in self-evaluation and self-care as the T2T strategy recommends.

The “Data management” function is designed for medical staff to manage the patients more conveniently and design the medical research. They can log in to the app platform website to collect and export data and carry out statistical analysis and big data mining. The app itself can also do simple statistics and management of data. For example, data such as EASI, POEM, and PP-NRS scores at the time points of before treatment, 2 weeks, 4 weeks, 12 weeks, and 6 months after treatment could be automatically generated into statistical reports to be presented in the form of histograms or curves. The app can also be further improved and updated to the new version through the analysis of users’ habits, and the function modules could be optimized with the high frequency of use and the feedback from both medical staff and patients.

### 2.3. Study Design

This is a single-centered, prospective, randomized controlled trial that tests the superiority of the implementation of a T2T strategy by application of an AIADMS app in patients with AD in terms of improvement of clinical outcomes. It follows the CONSORT statement (http://www.consort-statement.org/ accessed on 24 February 2025) and is conducted under the regulations of the Declaration of Helsinki. A flow diagram of this study is demonstrated in Figure 3.

#### 2.3.1. Participants

Inclusion criteria: patients diagnosed with moderate to severe AD, aged 2–75 years; be able to communicate in Chinese; with basic reading and writing skills; participants or the guardian have smartphones or pads and are familiar with use skills.

Exclusion criteria: mental illness; personality disorder; language barrier; hearing impairment; communication difficulties; with serious coexisting diseases, such as cardiopulmonary insufficiency, liver dysfunction, renal dysfunction, blood system diseases, tumors, or other diseases; other situations that are not suitable for participating in the clinical trial.

#### 2.3.2. Randomization and Blinding

According to the sequence of time wherein the participants are enrolled, after entering the screen number and the individual’s information, the computer-based randomized number prepared on the Internet and the allocated group can be retrieved on the website of the CRS. While the statisticians responsible for final analysis will be blinded to the treatment assignment, the participants, investigators, healthcare providers, research assistants, and the responsible physicians will not be blinded.

#### 2.3.3. Intervention

Participants will be allocated to the “App group” or the “Control group”.

In the app group, participants will be assisted in using the app during the process of management and follow-up at the scheduled time points, including 2 weeks, 4 weeks, 8 weeks, 12 weeks, 6 months, and 12 months after treatment, and the evaluation of five treating objectives including PP-NRS, EASI, SCORAD, POEM, and DLQI should be done on the day of follow-up.

In the control group, the diagnosis, treatment, and follow-up of participants will be carried out according to the current routine on a face-to-face basis. The time points of the participant follow-ups will be determined by the responsible dermatologist, and the evaluation of five treating objectives including PP-NRS, EASI, SCORAD, POEM, and DLQI will be done and recorded on the day of follow-up.

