#### 2.3.4. Outcomes

Primary outcome:

The primary outcome is the overall efficiency rate of treating objectives including PP-NRS, EASI, SCORAD, POEM, and DLQI at 12 weeks after treatment, which is calculated as “Total number of participants with effective treatment of 5 treating objectives/total number of participants *100%”. Criteria for effective treatment are as below: ① PP-NRS absolute score ≤ 4; ② EASI-50, EASI-75, or EASI ≤ 7; ③ SCORAD-50, SCORAD-75, or SCORAD ≤ 24; ④ POEM absolute score ≤ 7; ⑤ DLQI absolute score ≤ 5.

Secondary outcomes:The respective efficiency rate of PP-NRS, EASI, SCORAD, POEM, and DLQI, which is calculated as “Total number of participants with effective treatment of PP-NRS, or EASI, or SCORAD, or POEM, or DLQI/total number of participants *100%”;The economic consumption such as the travel expenses, expenses with lost working days, accommodation expenses, medical expenses, etc.;Satisfaction evaluation, defined as the assessment for the overall medical services by answering questions about their level of satisfaction with healthcare: 0 means completely dissatisfied, and 100 means very satisfied, and the participants or their guardians give a score between 0 and 100.

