#### 2.3.7. Statistical Analysis

Spss29.0 software will be used to analyze the data according to the principle of intent to treat. Demographic data are described by mean, standard deviation, frequency, median, percentage, etc. All data are tested for normal distribution, the *t*-test is used for continuous variables that conform to normal distribution, the chi-squared test is used for classified variables, and a nonparametric test is used for variables that do not conform to normal distribution. After 2, 4, 8, and 12 weeks of treatment, the sub item compliance rates of PP-NRS, EASI, SCORAD, POEM, and DLQI are analyzed by repeated measures of variance. *p* < 0.05 means that the difference is statistically significant.

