The study also relies on objective outcome measures like the Eczema Area and Severity Index (EASI), which offers standardized and quantifiable assessments of disease severity, reducing the influence of subjective judgment. Strict adherence to standardized treatment protocols and follow-up assessments across all groups will ensure consistency in care and data collection, minimizing variability and enhancing the reliability of the findings.

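### Section 2.3.3 sets a week-12 assessment for the app arm only, while the primary outcome needs one in both arms and other sections imply one

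*Protocol article*

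**What the plan says.** Section 2.3.3 (Intervention) treats the arms differently. The app arm has "follow-up at the scheduled time points, including 2 weeks, 4 weeks, 8 weeks, 12 weeks, 6 months, and 12 months after treatment", and the five scales are due on those days. For controls, "follow-up of participants will be carried out according to the current routine on a face-to-face basis". It adds: "The time points of the participant follow-ups will be determined by the responsible dermatologist". Their scores "will be done and recorded on the day of follow-up", with no week named.

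Other sections assume common timing:

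- Section 2.3.4 (Outcomes), with no arm restriction and no visit window: "The primary outcome is the overall efficiency rate of treating objectives including PP-NRS, EASI, SCORAD, POEM, and DLQI at 12 weeks after treatment". The rate is divided by the total number of participants.
- Section 2.3.7 (Statistical Analysis), under intent to treat and not limited to one arm: "After 2, 4, 8, and 12 weeks of treatment, the sub item compliance rates of PP-NRS, EASI, SCORAD, POEM, and DLQI are analyzed".
- The Discussion says that assessments are set at weeks 2, 4, 8 and 12 and names no arm. It later states: "Strict adherence to standardized treatment protocols and follow-up assessments across all groups will ensure consistency in care and data collection".

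The schedule of assessments (Figure 3) is not shown in the text available. No section says how a missing week-12 assessment is counted.

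**The concern.** The control schedule in 2.3.3 does not guarantee the data that 2.3.4 needs. A dermatologist who books a control at weeks 9 and 16 complies with 2.3.3, and that participant has no week-12 scores. The trial must then treat the outcome as missing or take it from another week. Either way, the trial arm becomes tied to whether and when the primary outcome is measured.

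Unequal ascertainment is plausible here. The app reminds its users of scheduled follow-up (section 2.2). The physicians who set control visit dates know the allocation (section 2.3.2). The Discussion reports 5 to 10 minutes of clinic time per patient, against at least 90 minutes for the full set of tools, a set that there also includes ADCT. The between-arm analysis at weeks 2, 4 and 8 has the same difficulty. An analysis plan can choose how to handle missing scores, but it cannot recover scores that were never collected.

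**Working it through.** **Inputs.** From section 2.3.5: control rate 35%, app rate 55%, 5% significance, power 0.80, 20% dropout, 116 per arm. From section 2.3.4: the denominator is all participants. Assumed, because the article gives only one overall dropout figure: missingness by arm, missing counted as not effective, and missingness unrelated to success within an arm.

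**The plan's own figure.** For two proportions, two-sided 5%, pooled variance, no continuity correction, with a mean rate of 0.45:

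n = [1.96·√(2·0.45·0.55) + 0.8416·√(0.35·0.65 + 0.55·0.45)]² / 0.20² = (1.379 + 0.580)² / 0.04 ≈ 95.9, so 96 per arm, as stated. The stated 116 follows from 96 × 1.20 = 115.2, rounded up.

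**No true effect, missing counted as not effective.** The observed rate in an arm is 0.35 × (1 − share missing). The chance of a false win for the app is 1 − Φ[(1.96·SE₀ − D)/SE₁]. D is the difference in observed rates, SE₀ the pooled standard error and SE₁ the unpooled one.

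Example, 10% (app) against 30% (control) missing:

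- App 0.35 × 0.90 = 0.315; control 0.35 × 0.70 = 0.245; D = 0.070.
- SE₀ = √(0.28·0.72·2/116) = 0.0590, and 1.96·SE₀ = 0.1156.
- SE₁ = √[(0.315·0.685 + 0.245·0.755)/116] = 0.0588.
- (0.1156 − 0.070)/0.0588 ≈ 0.775, so the chance is about 0.22.

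| Missing, app / control | Observed, app / control | Spurious difference | False win for app | Any p<0.05 |
|---|---|---|---|---|
| 20% / 20% | 28.0% / 28.0% | 0 | 2.5% | 5.0% |
| 10% / 20% | 31.5% / 28.0% | 3.5 points | 8.4% | 9.0% |
| 10% / 30% | 31.5% / 24.5% | 7.0 points | 21.9% | 22.0% |
| 20% / 40% | 28.0% / 21.0% | 7.0 points | 23.5% | 23.6% |
| 10% / 40% | 31.5% / 21.0% | 10.5 points | 44.3% | 44.3% |

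Exact binomial enumeration agrees to within 0.2 percentage points. The inflation comes from the inequality between arms alone. By symmetry, the same excess of missingness in the app arm would produce false losses for the app at the same rates.

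**If the planned effect is real.** With 10% / 30% missing, the observed rates are 0.55 × 0.90 = 49.5% and 0.35 × 0.70 = 24.5%. The true 20-point difference would be reported as 25 points.

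**The case against.** The strongest reply is that a common week-12 assessment is clearly intended. Section 2.3.4 sets the endpoint at 12 weeks without an arm restriction, the Discussion twice points to set or standardized assessments, and Figure 3, where a control-arm week-12 assessment would appear, cannot be seen. This stands in part: a reader might infer that nothing in the trial provides for a week-12 assessment of controls, and the documents do not support that. But section 2.3.3 is the only visible Methods text on control follow-up times, and it says something else. If Figure 3 does list week 12 for both arms, 2.3.3 contradicts it and still needs correcting.

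A reader might also infer that unassessed controls are scored as failures, to the app's advantage. That is not established. Dividing by all participants under intent to treat permits that reading. The 20% dropout allowance in 2.3.5 fits equally well with dropouts leaving the analysis, and a missing-data rule may sit in an analysis plan that is not shown. App participants can miss assessments too, and the Discussion itself names inconsistent app use as a limitation. The direction is therefore conditional: complete-case analysis or scores taken at other weeks could bias either way.

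Finally, more regular follow-up is part of what the app is meant to deliver, and control care is meant to be routine. That is right. The fault lies in the timing of the outcome assessment; a difference between arms in visit frequency is part of the intended contrast.

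**Conclusion.** The concern holds as a contradiction with consequences for the primary outcome. Section 2.3.3 cannot be reconciled, as written, with 2.3.4, 2.3.7 and the Discussion. If 2.3.3 is followed, arm and assessment timing are confounded on the primary outcome, whichever missing-data rule is used.

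The size is conditional. If missing counts as not effective, with a true 35% in both arms and 116 per arm, equal 20% missingness leaves the error rate at its nominal level. A 10 to 30 point excess of missing controls over 10% missing in the app arm raises false wins for the app from 2.5% to between about 8% and 44%. The upper end needs 40% of controls to be unassessed, a figure that nothing in the article supports or excludes. Under other handling, neither size nor direction can be given from the documents. The matter should be settled before enrolment.

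**What to change.** 1. In section 2.3.3, schedule an outcome assessment of all five scales at baseline and week 12 in both arms, with the same window and the same stated time origin. Keep it separate from the visits that the dermatologist chooses, so that routine control care is unchanged.
2. In sections 2.3.4 and 2.3.7, state how a missing week-12 assessment is counted, identically in both arms.
3. In section 2.3.7, limit between-arm comparisons at weeks 2, 4 and 8 to times assessed in both arms.
4. Align the two Discussion statements, and Figure 3 if needed, with the corrected section 2.3.3.

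The cost is a few sentences and one fixed research assessment at week 12 per control. The staff time is real: the Discussion puts the full set of tools (with ADCT) at 90 minutes or more and has three clinicians evaluate each participant. Controls also gain a contact outside strictly routine care. The primary outcome already requires this assessment, however, and with equal missingness the two-sided error rate stays at about 5%. No change in sample size follows.
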